## Abstract

**Background:**

Low levels of physical activity are associated with numerous adverse health outcomes, yet sedentary lifestyles are common among both children and adults. Physical activity levels tend to decline steeply among children aged between 8 and 12 years, even though children’s behavioral patterns are largely governed by familial structures. Similarly, parents’ activity levels have been generally reported as lower than those of nonparents of comparable age. For this reason, family-based physical activity promotion interventions are a potentially valuable and relatively underresearched method for mitigating physical activity declines as children develop into adolescents and for increasing physical activity in parents.

**Objective:**

This study aims to assess the efficacy, feasibility, and acceptability of a novel theory-based web-based physical activity promotion intervention among parent-child dyads in Finland who do not meet physical activity recommendations at baseline.

**Methods:**

Participants (target N=254) will be recruited from the general population using a panel company and advertisements on social media and randomly assigned to either an immediate intervention group or a waitlist control group. The intervention consists of 4 web-based group workshops over the course of 10 weeks, web-based tasks and resources, and a social support chat group. Data on physical activity behavior and constructs from the integrated behavior change model will be collected through self-report surveys assessing physical activity, autonomy support, autonomous motivation, attitude, subjective norm, perceived behavioral control, intention, self-monitoring, habit, and accelerometer measurements at baseline, post intervention, and 3 months post intervention. Exit interviews with participants will assess the feasibility and acceptability of the intervention procedures.

**Results:**

This study will reveal whether the intervention changes leisure-time physical activity among intervention participants relative to the control group and will examine the intervention’s effects on important theoretical predictors of physical activity. It will also yield data that can be used to refine intervention materials and inform further implementation. Trial recruitment commenced in September 2023, and data collection should be completed by December 2024.

**Conclusions:**

The planned intervention has potential implications for both theory and practice. Practically, the use of an entirely web-based intervention may have scalable future uses for improving physical activity in 2 key populations, while also potentially informing on the value of dyadic, family-based strategies for encouraging an active lifestyle as an alternative to strategies that target either parents or children independently. Further, by assessing change in psychological constructs alongside potential change in behavior, the intervention also allows for important tests of theory regarding which constructs are most linked to favorable behavior change outcomes.

**Trial Registration:**

ClinicalTrials.gov NCT06070038; https://clinicaltrials.gov/study/NCT06070038

**International Registered Report Identifier (IRRID):**

DERR1-10.2196/55960

## Introduction

### Overview

Low levels of physical activity in adult and youth populations are associated with an increased risk of physical and mental health conditions and a reduced quality of life. Conversely, regular physical activity participation is associated with reduced chronic disease risk and better psychological health and well-being [1]. Accordingly, the World Health Organization has published evidence-based guideline levels of physical activity required to realize these health benefits. The guidelines recommend that adults aged between 18 and 64 years participate in at least 75 minutes of vigorous physical activity, 150 minutes of moderate physical activity, or an equivalent combination of both per week, while children aged between 7 and 17 years are recommended to participate in at least 60 minutes of physical activity per day. Studies indicate that most people do not achieve these guideline levels of physical activity [2]. Further, studies have observed a sharp drop in physical activity participation in child and adolescent populations, followed by generally low participation levels into and throughout adulthood [3].

Given the steep decline in activity levels, as children transition into adolescence, the development and implementation of behavioral interventions to encourage an active lifestyle is a key target area for health promotion research. One strategy proposed to enhance the efficacy of behavior change strategies for children’s activity levels is to target the family unit rather than children themselves. Specifically, parents of preteen children retain a strong influence on their child’s behavior, both through their own activity levels [4,5] and through the opportunity to provide support for and foster motivation toward leisure-time physical activity behaviors [6,7]. Further, evidence indicates that children likely influence physical activity behaviors and beliefs in their parents, as parents tend to be less active than nonparents [8], often citing their children’s lack of motivation or support as a barrier to being physically active [9]. This evidence of within-family effects indicates the potential utility of dyadic interventions for both parents and children [10], using theory-driven, group-based behavior change strategies to bolster social support, foster motivation, and reduce the perceived barriers to behavior in both the parent and child. Yet, despite evidence for the potential utility of these strategies, few physical activity interventions have been applied for parent-child dyads, and those that have tend not to have a strong basis in behavioral theory and are seldom evaluated systematically [11], inhibiting meaningful conclusions on their efficacy. In response to the relative scarcity of theory-driven, family-based physical activity intervention programs, we aim to develop and test an intervention to promote physical activity in low-active parents and their children based on the integrated behavior change model, an approach that outlines the multiple determinants and potential targets for intervention derived from multiple theoretical perspectives [12].

### The Integrated Behavior Change Model

The integrated behavior change model draws from several well-established behavioral theories: self-determination theory [13], the theory of planned behavior [14], the health action process approach [15], and the reflective impulsive model [16]. Central to the model is that individuals’ quality of motivation, which reflects whether their behavior is consistent with the self-endorsed reasons, is highly influential in individuals’ intentions to perform physical activity and physical activity participation. This premise is derived from self-determination theory, which makes the distinction between autonomous and controlled forms of motivation. Autonomous motivation reflects an individual’s performing physical activity consistent with their own interests, choices, needs, and sense of personal involvement [13,17]. By contrast, controlled motivation reflects performing activities for externally referenced reasons, such as for rewards or out of obligation to others. Of critical importance when it comes to performing physical activity, individuals who perform physical activities for autonomous motives are more likely to form intentions to perform physical activity in the future and are more likely to develop routines and habits, which can translate to long-term physical activity persistence [18]. This is because those citing autonomous reasons for performing physical activity are likely to persist because their motivation emanates from themselves, while those whose motives are controlled will only persist as long as the external contingencies (eg, rewards and demands from others) persist. A key tenant of self-determination theory [17,19], is that autonomous motivation for physical activity can be fostered through the support of salient others, such as parents or teachers. For example, parents who display behaviors that indicate support for children’s autonomy and competence toward physical activity and demonstrate a sense of unconditional relatedness with their children for physical activities, are more likely to foster autonomous motives in their children toward performing physical activity in the future [6,7,20]. As such, enabling parents to display autonomy-supportive behaviors with respect to presenting, discussing, and performing physical activity with their children is likely an important strategy to promote physical activity participation in children and may be particularly valuable in family-based interventions aimed at promoting physical activity. It is also likely to be useful in parent-child dyads, where both parent and child can be encouraged to display behaviors that support each other’s autonomous motivation. This is supported in empirical data, where autonomy-supportive parenting has been associated with autonomous motivation in children as well as positive behavioral outcomes [21], including enhanced physical activity [6].

The integrated behavior change model also specifies the processes by which autonomous motivation leads to intention toward, and actual participation in, physical activity in the future. Specifically, individuals who are autonomously motivated toward a behavior are proposed to be more likely to form adaptive beliefs in favor of performing that behavior in the future [12,22-24] and, as a consequence, form an intention to perform physical activity in the future. Such beliefs are represented in the model by the belief-based attitude, subjective norm, and perceived behavioral control constructs from the theory of planned behavior [14], a prototypical theory that identifies the antecedents of intentional behaviors such as physical activity. The theory stipulates intention is the salient predictor of subsequent behavior, and intentions themselves are a function of attitudes (beliefs about the perceived likely affective or instrumental outcomes of engaging in a behavior), subjective norms (beliefs about where important others in one’s life would want them to engage in a behavior or not), and perceived behavioral control (beliefs about whether engaging in a behavior is under one’s own control or within their abilities). Research has demonstrated that these beliefs tend to be reliably related to physical activity intentions and participation, signaling their potential as modifiable constructs that could be targeted in intervention strategies aimed at promoting positive intentions toward, and actual participation in, physical activity. Accordingly, interventions based on the theory and targeting the belief-based constructs have shown efficacy in changing intentions and behavior [25]. For example, interventions presenting persuasive messages that highlight the advantages of behavior and downplay the disadvantages, targeting attitude change, or prompting practice that assists individuals in successfully mastering the target behavior and overcoming obstacles, targeting perceived behavior control change, have been shown to be effective in promoting intention and behavior change in physical activity contexts [26].

While there is evidence for the utility of interventions based on the recommendations of self-determination theory (eg, use of strategies like fostering autonomy support in influential others) or the theory of planned behavior (eg, providing persuasive communications targeting belief change), the integrated behavior change model also acknowledges that these strategies are often more efficacious in changing motivation or intention than changing behavior [27]. Recognizing the shortfall in the association between motivation and behavior, such as relatively modest intention-behavior relations observed in physical activity [28-32], other strategies that bolster intentions may be useful. For example, researchers adopting action control frameworks have suggested that leveraging [28,33] intervention strategies such as planning and self-monitoring may strengthen the intention-behavior relationship and increase the likelihood that individuals act on their good intentions when performing physical activity [15,34].

### Study Overview Objectives

Given the need for interventions to help children maintain physical activity levels as they transition into adolescence and to help parents become more physically active, our group used the integrated model as a starting point to develop a novel, remotely delivered dyadic physical activity promotion intervention. By applying the integrated behavior change model to a parent-child intervention, we aim to use and strengthen within-family dynamics to foster autonomous motivation and encourage physical activity in both parents and preteen children. In this protocol, we describe a planned randomized controlled trial for testing the effects of this intervention in a sample of insufficiently active Finnish-speaking parents and children.

## Methods

### Trial Design

The trial will adopt a randomized waitlist control design in which parent-child dyads are the unit of randomization. Families will be randomized on sign-up to either an intervention group that receives the intervention immediately after baseline data collection or to a waitlist control group that will receive the intervention after all outcome data have been collected.

### Participant Recruitment and Eligibility

Parent-child dyads will be recruited from the general Finnish population through direct contact with a panel company, through social media advertisements, and through posts on parenting discussion boards and forums. Individuals who responded to the advertisements were directed to a screening survey hosted on the Webropol platform. To be eligible for inclusion, dyads must consist of a parent or guardian aged >18 years and a child aged 8-12 years, and both dyad members need to be considered sedentary. Parents are considered sedentary if they were not active for at least 30 minutes a day on 5 or more days in the past week, and children are considered sedentary if they were not active for at least 60 minutes per day in the past week. Dyads will be excluded if either the parent or child reported having a medical condition or injury likely to prevent them from safely engaging in physical activity. People meeting the inclusion criteria can continue in the Webropol survey to read information about the trial and are then offered the opportunity to provide their contact details to opt-in to the trial.

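### The parent screening rule does not confine enrolment to parents below the activity recommendation, although the objective says that it does

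*Protocol article*

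**What the plan says.** The Abstract (Objective) gives the population as "parent-child dyads in Finland who do not meet physical activity recommendations at baseline". The Introduction (Study Overview Objectives) describes a sample of "insufficiently active Finnish-speaking parents and children".

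The Introduction (Overview) states the recommendations that these descriptions refer to. For adults: "at least 75 minutes of vigorous physical activity, 150 minutes of moderate physical activity, or an equivalent combination of both per week". For children: "children aged between 7 and 17 years are recommended to participate in at least 60 minutes of physical activity per day".

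Methods (Participant Recruitment and Eligibility) turns this into a screen. It requires that "both dyad members need to be considered sedentary". For parents, counted over the past week: "Parents are considered sedentary if they were not active for at least 30 minutes a day on 5 or more days". For children: "children are considered sedentary if they were not active for at least 60 minutes per day in the past week". No other section adds a check of parents' weekly minutes or of vigorous activity.

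**The concern.** The adult recommendation is a weekly sum that can be reached in any number of days and at either of two intensities. The parent screen counts days that reach 30 minutes. Doing 30 minutes on 5 days is one way to reach the weekly sum, but not the only way, so failing the screen's threshold does not mean falling short of the recommendation. Someone with a few long sessions, or a few short vigorous ones, would be labelled sedentary while meeting the target.

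Readers will take the parent result as applying to parents below the recommendation, because the objective says so. If an unknown share of enrolled parents already meets it, that description is wrong for them. Those parents may also have less room to improve on the primary outcome, self-reported leisure-time activity.

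**Working it through.** **Inputs.** From the Introduction (Overview): 150 moderate minutes or 75 vigorous minutes per week, or an equivalent mix. The ratio 150/75 = 2 makes one vigorous minute worth two moderate minutes. From Participant Recruitment and Eligibility: a parent is eligible if fewer than 5 days in the past week had at least 30 minutes of activity.

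**Formulas.** Moderate-equivalent minutes = moderate minutes + 2 x vigorous minutes; the recommendation is met at 150 or more. Qualifying days = number of days with at least 30 minutes; the parent is eligible if this is below 5.

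**Where the two rules agree.** The screen's threshold of 5 x 30 = 150 minutes reproduces the moderate figure. A parent at 5 x 30 moderate is excluded and meets the recommendation. A parent at 4 x 30 = 120 moderate is eligible and does not meet it.

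**Where they disagree.**

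| Weekly pattern | Qualifying days | Screen | Moderate-equivalent minutes | Recommendation |
|---|---|---|---|---|
| 4 x 40 moderate | 4 | eligible | 160 | met |
| 3 x 60 moderate | 3 | eligible | 180 | met |
| 2 x 75 moderate | 2 | eligible | 150 | met |
| 6 x 25 moderate | 0 | eligible | 150 | met |
| 3 x 25 vigorous | 0 | eligible | 2 x 75 = 150 | met |
| 2 x 40 vigorous | 2 | eligible | 2 x 80 = 160 | met |

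**Direction of the mismatch.** Suppose the screener counts only activity of at least moderate intensity. Every excluded parent then has at least 5 x 30 = 150 minutes and meets the recommendation, so every parent below the recommendation is eligible. The eligible set is the intended population plus some parents who already meet the target.

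**Children.** Both the recommendation and the screen use 60 minutes per day, so there is no mismatch.

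**The case against.** A short frequency item anchored at 5 x 30 = 150 minutes is a workable proxy in a web screener, and the article states openly how it defines sedentary. Children, half the sample, are screened against the quoted recommendation. Parents below the recommendation are enrolled, and baseline activity is recorded by questionnaire and accelerometer. All of this stands, and it limits the point to a mismatch between the stated and the admitted parent population.

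Three stronger readings are tempting, and the documents do not support them.

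- *That the trial misses its target population, or can say nothing about parents below the recommendation.* With activity read as at least moderate, all such parents remain eligible.
- *That the screen also wrongly excludes parents who do only light activity.* This depends on whether the survey item specifies intensity. The article summarises that item and does not show it.
- *That the parent effect is diluted by a known amount.* One could average the two effect sizes in the Power Analysis, (0.45 + 0.48)/2 = 0.465, and assume that 10% to 30% of parents already meet the target and gain nothing, giving 0.465 x 0.9 = 0.42 down to 0.465 x 0.7 = 0.33. The share is not in the documents. Zero gain is not plausible as a default, because the questionnaire counts occasions of activity and has no stated ceiling at the recommendation. Nor does the Power Analysis say that 0.465 is the effect in people below the recommendation. An effect on the 3-month rule for collecting 6-month data rests on the same premises.

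**Conclusion.** The point holds in limited form. On the protocol's own figures, the parent screen admits parents who already meet the weekly recommendation, while the objective says that enrolled dyads do not meet it. The conclusion rests only on the quoted recommendation and the quoted rule. The two-to-one weighting of vigorous minutes is not essential, since 3 x 25 = 75 vigorous minutes meets the vigorous target directly.

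Allocation is random, so the comparison between arms is not biased. The consequence lies in the population to which the parent result applies, and possibly in the room for improvement. The share of parents concerned cannot be computed from the documents, so no figure is put on either. The mismatch is worth correcting because it changes how the result may be described and the correction is cheap.

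**What to change.** 1. Reconcile the Abstract (Objective) and Study Overview Objectives with Participant Recruitment and Eligibility. State the parent population as parents active for at least 30 minutes on fewer than 5 days of the past week, and do not describe all of them as below the recommendation.
2. Report the share of parents at or above the weekly total on baseline accelerometer data, which already separate moderate from vigorous time.
3. Pre-specify one sensitivity run of the primary model in dyads whose parent is below the weekly total on those data. Label it as supportive.
4. Keep every randomised dyad in the primary intention-to-treat analysis.

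Step 1 is needed in any case, because a sensitivity analysis alone leaves the texts in conflict.

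**Cost.** A wording change, one descriptive figure and one additional model run on data already planned. The stated population becomes broader. The sensitivity subset also has limits. Under Study Procedures, baseline data are collected after randomisation, so device wear or return could differ by arm. The accelerometer is also a different instrument from the screening item, and the wear diary itself allows for exercise done without the device.

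Adding weekly-minutes items to the screener for dyads still to enrol is possible but debatable. It would change eligibility during enrolment and leave two differently screened cohorts, for a gain of unknown size.

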### Power Analysis

The projected sample size was estimated from a statistical power analysis conducted using G*Power (version 3.1; Heinrich-Heine-Universität Düsseldorf). The analysis assumed a small to medium effect size (Cohen *f*=0.235) for the intervention on our primary outcome variable, leisure time physical activity, calculated from an average of effect sizes from meta-analyses of self-determination theory–based interventions (Hedges *g*=0.45 [35]) and interventions targeting self-efficacy (Cohen *d*=0.48 [36]), with α set at .05 and statistical power set at .80 reveal a projected total sample size of 178 participants. We also assumed a projected 30% attrition rate in participants through the study based on similar trials [37], resulting in a sample of 254 participants (ie, 127 dyads) to be recruited at baseline.

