## Discussion

### Overview

This protocol presents a randomized controlled trial aiming to increase physical activity levels in inactive parent-child dyads within Finland, based on the integrated behavior change model. We hypothesize in this protocol that both parents and children will show increased levels of physical activity, our primary outcome variable, both at the immediate and 3-month postintervention stage, relative to a waitlist control group. Further, we hypothesize we will observe similar changes in the trial’s secondary outcomes, the psychological constructs of the integrated behavior change model (ie, autonomy support, autonomous motivation, attitude, subjective norm, perceived behavioral control, self-monitoring, intentions, and habit), in the intervention group relative to the waitlist control group.

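### The 80% power treats 178 individuals as independent; they are 89 dyads, so it fails for parents or children separately and holds for a pooled effect only at low within-dyad correlation

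*Protocol article*

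**What the plan says.** The Power Analysis section states this premise: "The analysis assumed a small to medium effect size (Cohen *f*=0.235) for the intervention on our primary outcome variable, leisure time physical activity". The effect is described as an average of two meta-analytic values, 0.45 and 0.48. Alpha is .05, and "statistical power set at .80 reveal a projected total sample size of 178 participants". Allowing for 30% attrition, the section ends by "resulting in a sample of 254 participants (ie, 127 dyads) to be recruited at baseline". A participant in this calculation is therefore one parent or one child.

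The Trial Design section says that "parent-child dyads are the unit of randomization". The Overview of the Discussion hypothesises that "both parents and children will show increased levels of physical activity, our primary outcome variable, both at the immediate and 3-month postintervention stage". The Data Analysis section puts within-dyad clustering, and clustering by delivery group, into the model for the primary outcome. The Power Analysis section contains no within-dyad correlation and no design effect, and it names no statistical test.

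**The concern.** A parent and a child from the same family share the allocation, the household and the workshops, so their outcomes are unlikely to be independent. The analysis model recognises this and the sample size does not. The hypothesis also speaks of parents and of children, and each role supplies only half of the 178.

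What is at stake is how the result will be read. If the effect in parents, or in children, turns out non-significant, a reader of the article will take it as a null from a trial with 80% power. The stated figure does not support that for a single role. For a pooled effect it does so only under a correlation that the article leaves unstated.

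**Working it through.** **Inputs from the protocol article.** Alpha .05; power .80; f=0.235, which is d=2×0.235=0.47 for two groups; 178 evaluable people; 30% attrition; 127 dyads recruited; two groups.

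**Assumptions.** Two-sided test and 1:1 allocation (neither is stated), so 44 and 45 completing dyads per arm. For the pooled effect, equal effect and equal variance in parents and children. All correlations are assumed.

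**1. Reproducing 178.** Noncentral F for independent observations, noncentrality λ=N·f².
- Numerator df 2: N=177 gives power 0.799; N=178 (λ=178×0.235²=9.83) gives 0.801. So N=178, exactly the stated figure.
- Numerator df 1 (plain two-arm comparison): N=144 gives 0.7998; N=145 gives 0.803. So N=145. At N=178 the power would be 0.877.
- Repeated-measures calculations for two groups (two or three visits, correlation 0 to 0.8, sphericity) gave between 14 and 130; none gave 178.

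So 178 is an independent-observations figure, with no allowance for dyads inside it.

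**2. Attrition.** 178/0.70=254.3 and 254×0.70=177.8, so the inflation is correct. In dyads, 127×0.70=88.9, or 89.

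**3. Power within one role.** Noncentral t with 87 df, critical value 1.988, noncentrality d·√(44×45/89)=4.717·d.
- d=0.47: noncentrality 2.217, power 0.592.
- d=0.465 (mean of 0.45 and 0.48): noncentrality 2.193, power 0.583.
- d=0.60: noncentrality 2.830, power 0.799. So 80% power in one role needs d of about 0.60.

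**4. Power for one pooled dyad effect.** The mean of two members with correlation ρ has variance σ²(1+ρ)/2, so the standardised effect is d/√((1+ρ)/2). With 44 and 45 dyads and 1 df:

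| Assumed ρ | Effect on dyad means (d=0.47) | Power, d=0.47 | Power, d=0.465 |
|---|---|---|---|
| 0.2 | 0.607 | 0.808 | 0.800 |
| 0.3 | 0.583 | 0.776 | 0.767 |
| 0.4 | 0.562 | 0.745 | 0.736 |
| 0.5 | 0.543 | 0.716 | 0.707 |

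At d=0.47 the pooled test keeps 80% up to ρ of about 0.22 (power 0.801). This agrees with the design effect: for pairs it is 1+ρ, and 178/145=1.23.

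**5. Gain from baseline adjustment.** Adjusting for a baseline with correlation r to follow-up divides the residual SD by 1/√(1−r²), that is, multiplies it by √(1−r²). With r assumed 0.5 and 0.6:
- Pooled, ρ=0.3: 0.47/√(0.65×0.75)=0.673, power 0.88; 0.47/√(0.65×0.64)=0.729, power 0.92. At d=0.465: 0.87 and 0.92.
- Per role: 0.47/√0.75=0.543, power 0.72; 0.47/√0.64=0.5875, power 0.78. At d=0.465: 0.71 and 0.77.

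**Side point.** The mean of 0.45 and 0.48 is 0.465, hence f=0.2325 rather than 0.235. With 2 df that moves 178 to 182, which is minor.

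**The case against.** The strongest reply is that the Data Analysis section plans one series of models holding both dyad members, with time and within-dyad clustering, so the natural primary test is pooled. The per-role figure belongs to separate, unadjusted follow-up comparisons that the article does not specify. On the pooled reading, the 178 exceeds the 145 of a 1-df test by enough to absorb a correlation of about 0.2, and a measured baseline could recover more. This largely stands, and it is why the shortfall must be stated as a range. It does not rescue the paragraph as written: the 80% is tied to no pooled test, no correlation and no baseline gain, and nothing in the text presents the surplus over 145 as a margin for dyads.

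Four stronger readings are tempting, and the article does not support them.
- A reader might infer that the trial succeeds only if parents and children are each significant, and multiply the powers. The hypothesis names both roles, but no such decision rule is given.
- A reader might infer that 2 df cannot be the intervention contrast. A condition-by-time test over three visits in two arms has (2−1)×(3−1)=2 df. Whether that lies behind 178 is unknown; the defect is only that the test is unnamed.
- A reader might infer that the rule on omitting 6-month data collection acts on a per-role null with 89 dyads. The rule in Study Procedures refers to the primary outcome at 3 months, without mention of role, and the 30% attrition applies through the whole study, so more than 89 dyads may be available then.
- A reader might subtract further power for delivery-group clustering. The article gives neither an intraclass correlation nor a group size, so no figure can be attached.

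**Conclusion.** The point holds in this form: the stated 80% rests on 178 independent individuals, while the design delivers 89 completing dyads. At the protocol's own d=0.47, unadjusted power is about 59% in each role (58% at d=0.465). For a pooled 1-df dyad effect it runs from about 81% at a within-dyad correlation of 0.2 to about 72% at 0.5.

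The per-role figure needs only 1:1 allocation, a two-sided test and no baseline adjustment. The pooled figures also need the assumed correlation and a common effect in both roles. It would be too strong to say that the trial as a whole has 59% power, or that the attrition arithmetic is wrong: the inflation from 178 to 254 is correct. What fails is the unqualified claim of 80% for this design and this hypothesis.

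**What to change.** Rewrite the Power Analysis paragraph; recruitment stays at 127 dyads.

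1. Restate power with the dyad as the unit (127 recruited, 89 completing). Give the pooled figure over a stated range of within-dyad correlation, and the per-role figure of about 59% at d=0.47 (80% only for d of about 0.60).
2. Name the test, with its numerator degrees of freedom, from which 178 was obtained.
3. Declare the baseline-adjusted pooled dyad effect as the powered test, at about 0.87 to 0.92 for an assumed within-dyad correlation of 0.3 and baseline correlation of 0.5 to 0.6. State these correlations as assumptions.
4. Report the parent and child effects separately as lower-powered, at about 0.71 to 0.78 under the same baseline assumption.

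The cost is one reworded paragraph and a less favourable power statement for the separate roles. No extra participants are needed.
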